### Statistical analysis

A full statistical analysis plan will be published online before the end of recruitment. All statistical analyses will be conducted according to the modified intention-to-treat principle considering all patients in the treatment groups to which they were randomly assigned, excluding cases lost to follow-up due to withdrawal of consent or cancelation of surgery. For both arms, the baseline characteristics will be expressed as counts and percentages, means and standard deviations, or medians and interquartile ranges, depending on normality of data distribution.

Data analysis will be performed blinded for the allocated study intervention. In all analyses, statistical uncertainties will be quantified with two-sided 95% confidence intervals. A two-sided *p*-value < 0.05 will be considered statistically significant. We will not adjust the *p*-value for multiple comparisons.

For the noninferioirty assessment of duration of ventilation, a one-sided noninferiority hypothesis test with a significance level of 0.025 and presented with a one-sided 97.5% confidence interval will be used. If noninferiority is confirmed, superiority will be tested considering a two-sided 95% confidence interval. Since the proposed approach will use a hierarchical closed-testing procedure examining a single confidence interval, no adjustment of the overall type I error will be done.

Statistical analysis will be performed using the free software program “R” (R Core Team, 2020, Vienna, Austria).

The effects of the intervention on quality of ventilation are analyzed and reported as done in previous studies of automated ventilation, i.e., the *time* spent in predefined zones of ventilation [17, 18]. As an add to the primary endpoint, next to *time* spent in predefined zones, we will also calculate *numbers* of breath in predefined zones. For details, see Appendix 1.

The impact of the intervention on ICU team staff workload is reported as in previous studies collecting data on alarms [12–14, 19].

All other endpoints, including duration of ventilation and ICU and hospital length of stay are reported as numbers and proportions.

Patient flows will be presented in a consolidated standard of reporting trials (CONSORT) flowchart.

Patients’ baseline characteristics will be presented per study arm. The proportion of patients who were treated according to their treatment assignment will be reported by treatment group.

Comparisons of the collected variables will be performed using *χ*^2^ tests for equal proportion, Student’s *t*-test for normally distributed data and Wilcoxon rank sum tests otherwise.

The database will be locked as soon as all data are entered and all discrepant or missing data are resolved—or if all efforts are employed and we consider that the remaining issues cannot be fixed. At this step, the data will be reviewed before database locking. After that, the study database will be locked and exported for statistical analysis. At this stage, permission for access to the database will be removed for all investigators, and the database will be archived.

No or minimally losses to follow-up for the primary and secondary outcomes are anticipated. Complete case analysis will be carried out for all the outcomes, that is, excluding patients with missing data in the outcome of interest. However, if any missing data is found for the primary outcome, a sensitivity analysis using multiple imputations and estimating equation methods will be performed.

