### Standard ventilation management

In the ICU, subjects are cared for by dedicated board-certified ICU team. Changes in treatment are implemented based on observations by ICU team and physicians and according to the recommendations in the local guideline for postoperative care. Automated ventilation is generally initiated within 10 min after ICU arrival, with automated adjustments of minute volume, PEEP, and FiO_2_ activated. Extubation is performed according to criteria described in the local protocol.

After arrival in the ICU, the attending caregiver initiates the ventilator mode of choice, using lung-protective ventilator settings, guided by blood gas analyses. Use of another automated mode is *not* allowed: only standard pressure-controlled ventilation or volume-controlled ventilation modes are allowed in passive patients and assisted breathing in active patients. *V*_T_ and RR, and PEEP and FiO_2_ are set and adjusted to keep etCO_2_ and PaCO_2_ in range. Typically, PEEP is limited to 5 to 12 cm H_2_O, FiO_2_ is limited to 30 to 100%. In case of a difference between PaCO_2_ and etCO_2_ of ≥ 5 mm Hg, the etCO_2_ target is adjusted. As soon as a patient displays spontaneous breathing efforts, the ventilator is switched from controlled to supported ventilation. The patient is extubated according to the local protocol; quantitative neuromuscular monitoring (e.g., train-of-four (TOF) monitoring) should be considered in case multiple doses of muscle relaxants are given in the operating room, or in the ICU––in those cases, before extubation residual curarization should be addressed (e.g., TOF > 0.9).

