### Intervention

The intervention tested is named “INTELLiVENT-ASV”, an automated ventilation mode available at Hamilton Medical AG ventilators (Hamilton Medical AG, Bonaduz, Switzerland) and intended to be used in patients that need ventilation in an ICU. INTELLiVENT-ASV is a fully automated mode of ventilation, targeting the lowest work and force of breathing, through breath-by-breath adaptation of *V*_T_ and RR, and PEEP and FiO_2_ based on patient activity, airway pressures and continuous pulse oximetry readings and end-tidal carbon dioxide monitoring. It also uses a weaning protocol and spontaneous breathing trials to facilitate weaning.

After arrival in the ICU, subjects start as soon as possible with INTELLiVENT-ASV. The attending caregiver initiates this automated ventilation mode, typically within 10 min after arrival in the ICU, when the results of the first blood gas analyses become available. Automatic adjustments for percentage of alveolar minute volume, PEEP, and FiO_2_ are activated and standard thresholds are set: PEEP is limited to 5 to 12 cm H_2_O, FiO_2_ is limited to 30 to 100%, and a “normal lung condition” is chosen. In case of a difference between PaCO_2_ and etCO_2_ of ≥ 5 mm Hg, the etCO_2_ target is shifted as described in the clinical guideline in use in the participating ICU. If clinically indicated, the target range for SpO_2_ can be manually adjusted. The options “Quick Wean” and “automated spontaneous breathing trials” are activated at start of ventilation by means of INTELLiVENT-ASV.

With INTELLiVENT-ASV, manually switching off one or more of the automated controllers by the attending caregiver (i.e., due to poor sensor signal quality) is allowed at any point during the study, in compliance with standard ventilation management of the participating ICU. According to a standard operating protocol, in case of a large discrepancy between SpO_2_ and SaO_2_ (SaO_2_ > 5% lower than SpO_2_), the automated FiO_2_ and PEEP controllers should be switched off, and in case of a minute ventilation of > 200% of the predicted minute volume, the minute volume controller should be switched off.

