### Minimization of bias

In order to prevent dropouts, randomization is performed shortly before the start of surgery as soon as it is certain the surgery will proceed and there is the availability of a ventilator that can be used for the study. Randomization will then be performed by local investigators using the Castor platform [www.castoredc.com]. Included patients will be randomly allocated in a 1:1 ratio to the INTELLiVENT group or to non-automated ventilation group. The allocation sequence will be computer-generated, using the Castor randomization module with permuted blocks of different block sizes, with a maximum block size of 8 and stratified per center.

Further minimization of bias will be achieved by involving at least two independent investigators per site. Investigator responsible for the preoperative and postoperative care cannot be kept blind due to the nature of the intervention tested. All analyses are preplanned, i.e., before closing of the database, and will be performed by an investigator that remains blinded for treatment allocation.

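### Randomisation is stratified by centre, but the only between-group tests the article names ignore centre; if centres differ, these tests are conservative and give up some precision

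*Protocol article*

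**What the plan says.** Under Minimization of bias: "Included patients will be randomly allocated in a 1:1 ratio", with a computer-generated sequence "with permuted blocks of different block sizes, with a maximum block size of 8 and stratified per center".

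The end of Statistical analysis names the tests for comparing the collected variables: chi-square "tests for equal proportion, Student’s" t-test for "normally distributed data and Wilcoxon rank sum tests otherwise". Neither centre nor any other covariate is mentioned.

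For duration of ventilation, the same section gives a one-sided non-inferiority test at 0.025 with a matching one-sided interval, but no estimator or model. It refers quality of ventilation to the method of earlier studies and Appendix 1, and workload to earlier studies. A fuller analysis plan is promised before the end of recruitment.

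On local practice, Standard ventilation management says: "Extubation is performed according to criteria described in the local protocol". Anaesthesia, sedation, pain and fluid management follow each centre's routine (Standard procedures beyond ventilator management). In the automated arm, however, "The options “Quick Wean” and “automated spontaneous breathing trials” are activated at start of ventilation" (Intervention).

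**The concern.** With stratified blocks the arms are nearly balanced within each centre, so differences in level between centres largely cancel out of the treatment contrast. A two-sample test does not know this: it estimates error from the pooled spread, which still contains the between-centre part. Its standard error is then larger than the true sampling error under the randomisation used.

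What is at stake is efficiency. Intervals are wider than they need be, and the test runs below its nominal error rate. This matters most for duration of ventilation, because that non-inferiority comparison sets the total of 328 patients against a margin of only 0.75 h.

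**Working it through.** **Inputs** (Sample size calculation): 164 per arm; SD 5.0 h; true difference −1.01 h; margin 0.75 h; alpha 0.025 (one-sided, per Statistical analysis); power 90%. The between-centre share of the total variance, ρ, is not in the document. I assume 0, 0.05, 0.10 and 0.20 and hold the total SD at 5.0 h.

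**The plan's own figure.** The distance from true difference to margin is 0.75 + 1.01 = 1.76 h. Then n = 2 × [5.0 × (1.960 + 1.282) / 1.76]² = 169.6, so 170 per arm, not 164. At 164 per arm, SE = 5.0 × √(2/164) = 0.552 h and power = Φ(1.76/0.552 − 1.96) = Φ(1.23) = 89.0%. The stated 164 is recovered (163 by the normal formula, 164 by the noncentral t) if the difference is 70% of the quoted 1.5 h, that is 1.05 h. That mismatch is a separate point; below I use the printed −1.01.

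**Formulas**, with a common additive centre effect and balance within centre:
- The true SE of the contrast is 0.552 × √(1−ρ). The unadjusted test uses 0.552, an overstatement by 1/√(1−ρ).
- Unadjusted one-sided error at the margin: 1 − Φ(1.96/√(1−ρ)).
- Unadjusted power: Φ((1.76/0.552 − 1.96)/√(1−ρ)).
- Centre-adjusted power: Φ(1.76/(0.552 × √(1−ρ)) − 1.96).

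| Assumed ρ | SE overstated by | Half-width, unadjusted / adjusted (h) | Unadjusted one-sided error | Power unadjusted | Power adjusted | Gap (points) |
|---|---|---|---|---|---|---|
| 0 | 0% | 1.08 / 1.08 | 0.025 | 89.0% | 89.0% | 0 |
| 0.05 | 2.6% | 1.08 / 1.05 | 0.022 | 89.6% | 90.5% | 0.9 |
| 0.10 | 5.4% | 1.08 / 1.03 | 0.019 | 90.2% | 91.9% | 1.7 |
| 0.20 | 11.8% | 1.08 / 0.97 | 0.014 | 91.5% | 94.6% | 3.1 |

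With adjustment, 90% power would need 170, 162, 153 or 136 per arm. If the true difference is −1.05 h, the gaps are similar: 0, 0.8, 1.5 and 2.7 points.

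**Simulation check.** I assumed 8 equal centres of 41 patients and blocks of 4, 6 and 8 (the document does not give the number of centres), with 2,000 trials per scenario. At ρ = 0.20, power was 92% unadjusted and 95% adjusted, with mean half-widths of 1.07 and 0.97 h. Rejection at the margin was 0.017 unadjusted and 0.029 adjusted; the latter is within simulation error of 0.025 (standard error √(0.025 × 0.975/2000) = 0.0035). At ρ = 0 the two analyses agreed (88.3% and 88.2%).

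The arithmetic covers a mean difference. The direction carries over to rank and proportion tests, but their size was not calculated.

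**The case against.** The strongest reply is that the article does not fix the analyses that matter most. Its sentence on tests is generic, the non-inferiority interval has no named estimator, the primary endpoint is referred to earlier studies, and a fuller plan could add centre. This stands in part. A reader might infer that every comparison is fixed as unstratified, and the text does not go that far. But the article does more than stay silent: it names tests, all of them ignore centre, and nothing in it points to another choice.

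Second, no between-centre variance is given, and the Discussion calls ventilation highly standardised in both arms, including during weaning. A reader might also infer from the local extubation rule that weaning is purely local. It is not, since the automated arm uses automated weaning functions. If local practice acts mainly in the control arm, centre effects differ by arm and the formula above is only approximate. This stands as a limit on the size. Centre differences remain plausible: the same Discussion says other care follows local guidelines and that the trial spans several countries and types of hospital.

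Third, the error is in the safe direction and the trial has reserve. Sizing used 5.0 h where earlier trials found 3.9 and 2.7 h; at 3.9 h, 164 per arm would give about 98% power with the same difference and margin. The primary endpoint needs 110 per arm. This stands too, though the 3.9 h comes from a single-centre trial and so contains no between-centre variance.

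**Conclusion.** The point holds as a mismatch between the randomisation and the named tests, with a modest and conservative effect. For between-centre shares of 5 to 20%, intervals are about 3 to 12% too wide and power for duration is about 1 to 3 points below what adjustment would give. With no centre differences there is no loss. These sizes rest on assumed shares, a common additive centre effect, near balance within centre and a total SD of 5.0 h.

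A reader might infer that the unadjusted tests push power below plan. The figures do not support that: at 164 per arm unadjusted power rises from 89.0% to 91.5% as the centre share grows, and the 1.0-point shortfall at zero comes from the printed −1.01 h, not from ignoring centre. Power is lost only relative to an adjusted analysis. Nor is a false claim of non-inferiority made more likely. The reason to act is that the gain in precision needs no extra patients.

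**What to change.** In Statistical analysis and in the full analysis plan, before unblinding, make the main analyses centre-adjusted:

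- Duration of ventilation: a linear model with treatment and centre, giving the mean difference and the interval to be compared with the 0.75 h margin.
- Zone proportions, lengths of stay and workload: models with centre as a fixed effect or random intercept, or the van Elteren test where ranks are used.
- Binary endpoints: a centre-stratified test such as Cochran–Mantel–Haenszel.

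Keep the unadjusted tests as supportive analyses. Centre is already recorded as the randomisation stratum, so the cost is analysis wording only: no new data, no extra patients and no change in conduct.

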### Subgroups analyses

There are no subgroup analyses planned, and a more detailed analysis plan will follow at the end of the study, before cleaning and closing of the database. The so-called “updated and finalized statistical analysis plan” will be outlined in a protocol amendment.

### Trial organization

The coordinating center and sponsor is the Medical University of Vienna. The steering committee is composed of the principal investigator, the coordinating investigator, the local investigators, and international experts of ventilation who contribute to the design and revisions of the study protocol.

The principal investigator, along with coordinating investigators, monitors, and auditors, will be granted access to the data and documents. A team of committed investigators will manage and coordinate patient recruitment and data collection daily. Investigators from the sponsor center will maintain frequent communication with other trial centers. Strict adherence to the trial protocol and relevant regulatory requirements will be ensured by the investigators.

An independent data safety monitoring board (DSMB), consisting of renowned, independent anesthesiologists, watches over the ethics of conducting the study in accordance with the Declaration of Helsinki and monitors safety parameters and the overall conduct of the study. The DSMB is composed of four independent experts.

The DSMB will meet after 50% of subjects are included or at least within 9 months after the first patient is enrolled. Subsequent to this meeting, the DSMB will meet virtually every 6 months. The DSMB will monitor safety by monitoring the specific safety endpoints as described above. The DSMB will monitor protocol compliance of both treatment strategies. The DSMB will review the overall status of the program: number of patients enrolled overall and, in each center, adherence to the protocol overall and by each center. All unexpected non-study related (S)AEs will be reported to the DSMB twice a year. Study-related SAEs will be sent to the DSMB, as soon as possible but at latest within 7 days after being received by the coordinating center. The advice of the DSMB will only be sent to the sponsor of the study. Should the sponsor decide not to fully implement the advice of the DSMB, the sponsor will send the advice to the reviewing medical ethical committee, including a note to substantiate why (part of) the advice of the DSMB will not be followed.

A safety analysis will be performed at 50% of patients included. Results of this safety analysis will be presented to the members of the DSMB and will be discussed at a planned meeting.

The study will be terminated if, as a result of our intervention, a disproportional amount of (serious) adverse events occur and causality between the intervention and adverse events is assumed. Interim analysis on safety will be performed and the results will be communicated, blinded for randomization, to the DSMB. Any deviation from the protocol, other than eight preapproved protocol deviations, are considered protocol violations. Protocol violations are to be reported and will be discussed with the DSMB.

## Discussion

POSITiVE II tests the hypothesis that automated postoperative ventilation by means of INTELLiVENT-ASV is superior to non-automated postoperative ventilation by means of pressure-controlled ventilation or pressure support ventilation with respect to quality of breathing *and* ICU team staff workload, and non-inferior with respect to duration of ventilation and lengths of stay in ICU in post-cardiac surgery patients. Thus far, there has been only one randomized clinical study that answered the question whether INTELLiVENT-ASV is superior to non-automated ventilation with respect to the quality of breathing [17]. This study, however, had a single-center design and preferably its findings are to be confirmed in an international, multicenter trial. We ourselves are performing another international multicenter trial, named ACTiVE, that will test a comparable hypothesis—a study that enrolls patients in the Netherlands and Switzerland [15]. ACTiVE is a study in general ICU population, and excluding patients included in this current study as one major inclusion criterium of ACTIVE is an expected need invasive ventilation for 24 h or more.

The automated mode tested in this study uses breath-by-breath adjustments for more lung-protective ventilation. With that, the risk for ventilator-induced lung injury could be reduced, eventually leading to better patient outcomes. We will capture breath-by-breath data to test the primary hypothesis.

In critically ill patients, even when ventilation last only some hours, it is recommended to use an appropriate low *V*_T_, to titrate PEEP and inspired fraction of oxygen by means of a PEEP/FiO_2_ table, to target a lower driving pressure, and to avoid both hyperoxia and hyperoxemia. This can be challenging and is time-consuming, especially when ICU teams are less experienced in invasive ventilation. Automated modes have the potential to reduce the time teams spent at the ventilator and the amount of alarms related to ventilation teams have to respond to––however, these modes may also be more difficult to set and “supervise”. One single-center randomized clinical study in Belgium [14] and single-center observational study in France showed that INTELLiVENT-ASV requires fewer manual interventions at the ventilator [13]. One recent single-center observational study in severely ill and difficult to ventilate COVID–19 patients in Switzerland showed that the number of manual interventions at the ventilator was half of that with conventional ventilation [12]. The second hypothesis tested, therefore, is that automated ventilation by means of INTELLiVENT-ASV reduces ICU team staff workload. For this, we capture data using a number of alarms and manual ventilator settings approach.

We will also compare clinically relevant clinical outcomes, duration of ventilation, and lengths of stay in the ICU. These endpoints are chosen for the following reasons: duration of ventilation can be seen as one important patient-centered endpoint: discomfort for patients is reduced with a shorter duration of ventilation—length of stay is an important ICU-centered endpoint, as an increase in ICU stay may translate in a lower number of ICU beds available for care for other patients, and higher costs. Of note, we do not expect a difference in duration of ventilation and lengths of stay in the ICU between the groups.

Ventilation in both groups is highly standardized, in the intraoperative phase during anesthesia and in the ICU when the patient is weaned from invasive ventilation. Other parts of care follow strict local clinical guidelines. POSITiVE II aims at minimizing bias by using concealed allocation and an intention-to-treat analysis with a pragmatic protocol that can be strictly adhered to. POSITiVE II is performed in several European countries, in different types of hospitals, making the results generalizable.

In summary, POSITIVE II is designed to confirm the findings of an earlier single-center study, whether automated ventilation by means of INTELLiVENT-ASV is superior to non-automated ventilation by means of conventional ventilation, with respect to quality of breathing and ICU team staff workload. The results of this study can help ICU teams in their choices regarding the use of automated ventilation in the postoperative care setting.

## Trial status

Protocol version 1.2; January 29, 2024.

Recruitment: Estimated recruitment start will be on May 1, 2024. The anticipated recruitment completion is in August 2025.

## Data Availability

The full trial protocol and informed consent materials are available on any reasonable request to the corresponding author. The final trial dataset and the code for statistical analysis will be accessible by non-commercial partners upon request. A full monitoring plan is obtainable on reasonable request.

